### Data management

Completed personal data or other documents containing protected personal health information will be kept in a locked file at the principal investigator office in every centre. Data will be entered into an electronic de-identified database by authorized study team members, and checked for completeness and accuracy. Access to data with identifiers will be restricted to authorized study team members and authorities. Electronic data will be stored on a secure server regulated by the local research institute (IDISNA). Identifiable data will be destroyed 10 years after study finalization or 5 years after last publication.

### Detailed description of the intervention

Participants will be randomly assigned to the following groups.

#### Usual care group (control)

Participants randomly assigned to the usual care group will receive normal outpatient care, including physical rehabilitation when needed.

#### Multicomponent VIVIFRAL exercise group

The multicomponent physical exercise programme will be the VIVIFRAIL programme which was developed in Europe (Erasmus+ programme of the European Union). The VIVIFRAIL [26, 27] multicomponent exercise intervention programme consists of resistance training, gait re-training and balance training, which appear to be the best strategy for improving gait, balance and strength, as well as reducing the rate of falls in older individuals and consequently maintaining their functional capacity during ageing [26, 27]. This type of intervention has also been proven as the most effective to delay disability, cognitive impairment and depression [33] as well as effective to reverse the functional decline associated with acute hospitalization in very old patients [28].

The VIVIFRAIL exercise programme offers a general guideline to design a multicomponent physical exercise programme for frailty and falls treatment and prevention among people aged older than 70 years [26]. The programme is personalized, depending on the older person’s functional capacity level (serious limitation, moderate limitation and slight limitation as evaluated by the SPPB and a walking speed test) and the risk of falling. VIVIFRAIL works on the following components of physical fitness: arm and leg strength and power, balance and coordination to prevent falls, flexibility and cardiovascular endurance (i.e. walking).

All of the exercises outline the procedure, guidelines for starting, frequency and progression to be able to correctly monitor the instructions prescribed to the patient and improve their health [26].

To individualize the exercise programme we will assess the initial functional capacity and determine the risk of falling. Different functional capacity levels will be determined based on the scores obtained from the Short Physical Performance Battery Test (SPPB) and the 6-m gait velocity test (GVT) (see Fig. 3), with each leading to the recommendation of a certain customized multi-component physical exercise programme (Program A, B, C1, C2 or D) (see Fig. 3). Two sub-types will be defined in order to more accurately recommend a particular cardiovascular endurance programme for the group with slight limitation (frail/pre-frail) based on the maximum time they can walk without help. If the person can walk for 10–30 min, they are known as C1; and if they can walk for 30–45 min, they are known as C2 [26].

This classification will be complemented according to the risk of falling, assessed by the answer to some simple questions (see Fig. 3). If a risk for falling is detected, the frequency of the exercise will be increased and some additional measures will be adopted, as depicted in the lower part of the right-hand side of Fig. 3. Finally, the participant will be assessed for potential contraindications or need of medical evaluation (left-hand side of Fig. 3) [26].

**Fig. 3 Fig3:**
[figure not shown]
Classification by allocation of the participant to a physical exercise group by the SPPB, gait speed and risk of falls. Modified from Izquierdo et al. [26]

Once the patient has been assigned to one of the six categories, a multicomponent programme taking 12 weeks will be implemented. The general characteristics of the different programmes are shown in Fig. 4.

**Fig. 4 Fig4:**
[figure not shown]
Classification by allocation and examples of exercises of the participant according to a functional level group by the SPPB, gait speed and risk of falls. Modified from Izquierdo et al. [26]

##### Resistance training

Sets and repetitions:◦ The session should begin by performing two sets of 10 repetitions (i.e. 10 repetitions of the selected movements).◦ The goal is to perform three sets of 12 repetitions.◦ A 1-min to 3-min break should be taken between exercises.◦ The exercises should be performed on 3 days per week.Intensity and progression:◦ For weight exercises, a weight or resistance band should be chosen that will allow the patient to perform the exercise without interruptions at least 30 times but with a certain degree of effort to complete the activity. The first step will be to determine the exercise or weight that allows them to do the exercise properly about 30 times without stopping yet makes them feel as though they have made an effort by the end.◦ To be effective, this programme should be followed for 12 weeks. After that time, the tests (the SPPB, GVT and assessment for determining risk of falls) should be repeated.Strength and power exercises are shown in Izquierdo et al. [26].

##### Cardiovascular training

Sets and repetitions:◦ When the elderly person improves their muscular strength, the cardiovascular exercise programme shall begin.◦ Walk, alone or with help at usual walking pace, until you are able to walk for 1 min without help.◦ For example:▪ Walk 5–10 s, rest 10 s.▪ Repeat five to seven times.▪ +▪ Walk 10–15 s, rest 20 s.▪ Repeat five to seven times.◦ Begin by walking for 4 min until you are able to walk for 15 min.◦ Begin by walking for 8 min until you are able to walk for 30 min.◦ Walk in sets of 15 min each, resting for 30 s between sets.Cardiovascular protocol and exercises in detail according to function are shown in Izquierdo et al. [26].

##### Balance training

Sets and repetitions:◦ Remain in the same position and count to 10 (progress up to 30) with each leg. Rest no less than 1 min and no more than 3 min. Repeat with each leg.◦ +◦ Walk one set of 10 steps. Stop and rest for 10 s without sitting. Rest no less than 1 min and no more than 3 min. Repeat.◦ +◦ Walk in a relaxed way and step over the obstacles. Set up five obstacles to begin. When you finish the walk, begin again. Repeat eight times.Intensity and progression:◦ Change the position of your arms; cross your arms or make a cross shape, for example.◦ Do the exercises on different surfaces; on a rug, for example.◦ Close your eyes, but only if someone is near to help you.Balance exercises are shown in Izquierdo et al. [26].

##### Flexibility

Sets and repetitions:◦ Two sets of three repetitions (remain in the same position for 10 s).Intensity and progression:◦ Stretch until you feel a bit of tension and then remain in the same position for 10–12 s.◦ Stretch without creating any excessive muscular elongation or articular tension.◦ Every day.◦ After the muscular strength and power or cardiovascular exercises.Flexibility exercises are shown in Izquierdo et al. [26].

Materials will be also provided to the caregivers and the participants in the Spanish language. All of the materials to be used will be properly adapted to the focused population. This exercise programme has recently launched the Vivifrail App for IOS and Android operating systems, which enables health professionals to assess the functional ability of elderly subjects and help them to prescribe a tailored multi-component physical exercise programme [26, 27] (www.vivifrail.com).

### Outcome measures

#### Primary outcome

The primary outcome measure is the change in functional and cognitive status during the study period. The functional capacity of patients will be evaluated by the Short Physical Performance Battery (SPPB) [34], which evaluates, balance, gait ability and leg strength using a single tool. The total score ranges from 0 (worst) to 12 points (best). The SSPB test has been shown to be a valid instrument for screening frailty and predicting disability, institutionalization and mortality. A total score of less than 10 indicates frailty and a high risk of disability and falls. A 1-point change in the score has clinical relevance [35, 36].

#### Secondary outcomes

Loss of handgrip in the dominant hand is a useful tool for the measurement of functional capacity. This characteristic is a strong predictor of disability, morbidity and mortality as well as one of the components of Fried’s frailty phenotype [4]. Furthermore, the functional status of patients will also be assessed at recruitment with the Barthel Index [37], an international and validated tool of disability. The score ranges from 0 (severe functional dependence) to 100 (functional independence). At baseline, gait ability will be assessed using the 6-m gait velocity test (GVT). Starting and ending limits will be marked on the floor with tapelines for a total distance of 8 m. Participants will be instructed to walk at their self-selected usual pace for two attempts. The best result of both trials will be registered. The first and last metre, considered the warm-up and deceleration phases, respectively, will not be included in calculations of the gait assessment. Dual-task conditions (gait evaluation during the simultaneous performance of a cognitive task) have recently been recognized as a sensitive assessment method for interactions among cognition, gait, falls and frailty. Changes in gait parameters (i.e. gait velocity and gait variability) while performing a dual-task test (dual-task cost) may be early predictors of fall risk [38, 39] and may be useful tools for functional evaluations in frail older patients. Exercise can modify the dual-task cost and, consequently, the fall risk and functional capacity [40]. The dual-task paradigm [37] will be used in the 6-m habitual GVT. Two trials will be conducted to assess gait velocity while the patient is performing a verbal or counting task (verbal GVT and arithmetic GVT, respectively). During the verbal dual-task condition (verbal GVT), we will measure gait velocity while participants are naming animals aloud. During the arithmetic dual-task condition (arithmetic GVT), we will assess gait velocity while participants are counting backwards aloud from 100 in ones. The cognitive score will be measured by counting the number of animals named (dual-task with verbal performance) or determining how many numbers were counted backwards (dual-task with arithmetic performance). Isometric upper limb (dominant hand grip) and lower limb (right knee extensors and hip flexors) muscle strength will be measured using a manual dynamometer. Maximal dynamic strength will be assessed using the 1RM test in the bilateral leg press exercise using exercise machines (Matrix, Johnson Health Tech, Ibérica, S.L., Torrejón de Ardoz, Spain; and Exercycle S.L., BH Group, Vitoria, Spain). In the first assessment, the subjects will warm up with specific movements for the exercise test. Each subject’s maximal load will be determined in no more than five attempts, with a 3-min recovery period between attempts. After the 1RM values are determined, the subjects will perform 10 repetitions at maximal velocity and at intensities of 50% of 1RM to determine the maximum power (W) and the loss of power during the 10 repetitions in the leg press exercise [41]. The power will be recorded by connecting a velocity transducer to the weight plates (T-Force System, Ergotech, Murcia, Spain). During all neuromuscular performance tests, strong verbal encouragement will be given to each subject to motivate them to perform each test action as optimally and rapidly as possible. Distribution of the training sessions throughout the day should minimize cumulative fatigue and help to maintain adherence. Adherence to the exercise programme will be documented in an individual daily log of the sessions. Changes in cognitive-affective status after the intervention will be measured using the Spanish validated versions of the Minimental Cognitive Exam (MEC-Lobo) [42] in the case of dementia and the MOCA [43] in the case of MCI. The Yesavage GDS [44] and Trail Making part A [45] will be performed to assess depression and executive dysfunction. During functional tasks (such as balance, gait and rising from a chair) and cognitive evaluations (dual tasking), an inertial sensor unit (IU) will be attached over the lumbar spine (L3) to record the acceleration data in control and intervention participants [46, 47]. Primary and secondary variables are presented in Table 1.

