**Methods/design:**

This study is a multicentre randomized clinical trial to be conducted in the outpatient geriatrics clinics of three tertiary hospitals in Spain. Altogether, 240 patients aged 75 years or older being capable of and willing to provide informed consent, with a Barthel Index ≥ 60 and mild cognitive impairment or mild dementia, pre-frail or frail and having someone to help to supervise them when conducting the exercises will be randomly assigned to the intervention or control group. Participants randomly assigned to the usual care group will receive normal outpatient care, including physical rehabilitation when needed. The VIVIFRAIL multicomponent exercise intervention programme consists of resistance training, gait re-training and balance training, which appear to be the best strategy for improving gait, balance and strength, as well as reducing the rate of falls in older individuals and consequently maintaining their functional capacity during ageing.

The primary endpoint is the change in functional capacity, assessed with the Short Physical Performance Battery (1 point as clinically significant). Secondary endpoints are changes in cognitive and mood status, quality of life (EQ-5D), 6-m gait velocity and changes in gait parameters (i.e. gait velocity and gait variability) while performing a dual-task test (verbal and counting), handgrip, maximal strength and power of the lower limbs as well as Barthel Index of independence (5 points as clinically significant) at baseline and at the 1-month and 3-month follow-up.

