Frailty according to the Fried criteria	X			
Montreal Cognitive Assessment (MOCA)—only for mild cognitive impairment	X		X	X
Categorical scale of pain		X		X
Geriatric Depression Scale of Savage (GDS)		X		X
Minimental Cognitive Exam (MEC-Lobo)		X	X	X
Gait velocity test (GVT)		X	X	X
Dual task (verbal and counting GVT)		X	X	X
Maximal isometric force of handgrip, knee extension and hip flexion		X	X	X
Isaacs Set Test		X		X
Quality of Life (EQ-5D)		X		X
Trail Making Test (TMT—Part A)		X	X	X
1RM (leg press)		X	X	X
Muscle power at 50% 1RM in leg press		X	X	X
Drugs, geriatric syndromes and psycho-behavioural symptoms		X		X
Cumulative Illness Rating Scale for Geriatrics (CIRS-G)		X		
Functional Activities Questionnaire (FAQ)		X	X	X
Mini Nutritional Assessment (MNA)		X		
Acceleration data: gait kinematic parameters (regularity, variability, cadence), Five Times Sit to Stand Test (peak power, impulse) and balance parameters (power spectrum, area)		X	X	X
Rate and risk of falls		X	X	X
Mortality		X	X	X
Admission and readmission to hospital		X	X	X
Institutionalization		X	X	X

Basic sociodemographic data of the participants will be collected in the baseline visit. All adverse events, including those related to exercise such as muscle pain, fatigue and general aches and pains, will be recorded in an “adverse events diary” during follow-up visits and telephone calls by the training and testing staff, and by self-report during the study period. The study flow diagram is shown in Fig. 2. The time at which different variables (primary and secondary) will be measured is presented in Table 1. The protocol employs relevant standard protocol items for clinical trials according to the SPIRIT 2013 statement (Additional file 1) [29] and follows the CONSORT statement [30] for transparent reporting. The trial is registered at ClinicalTrials.gov (identifier number iNCT03657940), and the status is recruitment.

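### The dual-task cognitive score is an untimed count over a fixed-distance, self-paced walk, so it moves inversely with the gait speed that the programme aims to raise

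*Protocol article*

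**What the plan says.** All of the following is in the protocol article.

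- **Setting of the task (Secondary outcomes).** The dual task is embedded in the gait test: "The dual-task paradigm [37] will be used in the 6-m habitual GVT". That test covers a fixed distance: "Starting and ending limits will be marked on the floor with tapelines for a total distance of 8 m". The first and last metre are left out of the gait calculation, which leaves 6 m. The pace is free: "Participants will be instructed to walk at their self-selected usual pace for two attempts".
- **Gait result (Secondary outcomes).** In the verbal condition, "we will measure gait velocity while participants are naming animals aloud". The arithmetic condition does the same with counting down from 100.
- **Cognitive result of the same walk (Secondary outcomes).** "The cognitive score will be measured by counting the number of animals named (dual-task with verbal performance" for the verbal task, and "determining how many numbers were counted backwards (dual-task with arithmetic performance" for the arithmetic task. No fixed duration, time denominator or correction for walking time is given.
- **Endpoint status of gait under dual task (Abstract, Methods/design).** The secondary endpoints include "changes in gait parameters (i.e. gait velocity and gait variability) while performing a dual-task test (verbal and counting".
- **Timing (Table 1).** The line "Dual task (verbal and counting GVT" is marked at baseline, 1 month and 3 months.
- **Analysis (Statistics and sample size).** Quantitative outcomes are compared by ANCOVA on the post-intervention value, with study group as the main effect and the pre-intervention value as covariate.
- **Expected effect (Multicomponent exercise group).** The programme is chosen because it is thought best for improving gait, among other things.

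**The concern.** A count is a fair measure of performance when every patient has the same time to respond. Here the distance is fixed and the time is not. A patient who walks faster has fewer seconds in which to name animals or count, and a patient who slows has more. The score therefore carries the reciprocal of gait velocity, which is the other result of the same walk and one that the intervention is designed to change.

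The distortion is linked to treatment. It arises after randomization, through the intended effect on gait, and works against whichever arm ends up faster. Adjusting for the baseline count does not remove it: the baseline count reflects baseline speed, whereas the distortion comes from the change in speed, which may differ between arms.

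At stake is how the dual-task results are read. A true gain in responses per second could be hidden, or a trade of cognition for speed could be inferred where none took place.

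**Working it through.** The plan gives no figure on this point, so there is none to reproduce. The check is algebra plus illustrative speeds.

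**Inputs from the article:** fixed distance D (6 m timed, 8 m walked); self-selected pace; score = count.

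**Inputs assumed, because the article gives none:** dual-task speeds from 0.4 to 0.7 m/s and a gain of 0.1 m/s.

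**Step 1: form of the score.** With r responses per second and speed v, walking time = D / v and count = r × D / v.

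**Step 2: change at a constant rate.** If speed goes from v0 to v1 and r stays the same, the relative change in count is v0 / v1 − 1. Neither r nor D appears, so the percentage is the same for fast and slow responders and for 6 m or 8 m.

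**Step 3: change when the rate also improves.** If r rises by a fraction g, the relative change is (1 + g) × v0 / v1 − 1. The count stays level only if g = v1 / v0 − 1.

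| Speed (m/s) | Time over 6 m (s) | Change in count, rate constant | Change in count, rate +10% | Rate gain needed to hold the count |
|---|---|---|---|---|
| 0.4 to 0.5 | 15.0 to 12.0 | 0.4/0.5 − 1 = −20.0% | 1.1 × 0.800 − 1 = −12% | +25.0% |
| 0.5 to 0.6 | 12.0 to 10.0 | 0.5/0.6 − 1 = −16.7% | 1.1 × 0.833 − 1 = −8% | +20.0% |
| 0.6 to 0.7 | 10.0 to 8.6 | 0.6/0.7 − 1 = −14.3% | 1.1 × 0.857 − 1 = −6% | +16.7% |

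As an example in counts, at an assumed 0.6 responses per second a patient who goes from 0.5 to 0.6 m/s drops from 0.6 × 12 = 7.2 to 0.6 × 10 = 6.0 responses.

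**Step 4: the reverse case.** A patient who slows from 0.5 to 0.4 m/s at a constant rate gains 0.5/0.4 − 1 = +25% in count.

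**Step 5: after the fix.** Count divided by walking time is (r × D / v) / (D / v) = r. At an unchanged response rate the score changes by 0% at any speed.

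The direction of the link follows from the definition alone. Only the percentages depend on the assumed speeds.

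**The case against.** Five points can be made on the other side.

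1. **The count is not named as a separate endpoint.** The abstract lists gait velocity and gait variability under dual task, Table 1 lists a gait velocity test, and Secondary outcomes assigns cognitive-affective change to MEC-Lobo, MOCA, the depression scale and TMT-A. This stands. A reader might infer that the trial will report a gait benefit as cognitive worsening. The article does not support that: it nowhere says that the count will be compared between arms or read as evidence of cognitive change.
2. **The derivation may be left to documents not shown.** The article does not say that the raw count is analysed without adjustment, and a later document could divide it by time. That is possible. But the article does state how the score is measured, and that definition has no time element, so the point concerns something stated and not something omitted.
3. **A faster patient need not score lower.** This stands. The fall requires that the response rate rise by a smaller proportion than speed. The trial hopes for gains in both gait and cognition, so the net direction cannot be known in advance.
4. **The size is assumed.** This also stands. Each scenario is a change in one patient of 17% to 25% in speed. The effect on a trial comparison would depend on the difference between arms in speed change, which the article does not allow one to estimate.
5. **The rate is not perfectly neutral.** If a patient produces a limited set of animals early and then stops, the same count in a shorter walk gives a higher rate: from 0.5 to 0.6 m/s, 0.6/0.5 − 1 = +20%. This is a real limitation, most plausible for animal naming, and it is the reason to report count and walking time beside the rate.

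**Conclusion.** The concern holds in a limited form. The stated score is mechanically and inversely tied to dual-task gait velocity, and the planned baseline-adjusted ANCOVA does not break that tie. When the response rate is unchanged or rises proportionally less than speed, the count falls although performance per second is unchanged or better. Under the assumed speeds, a gain of 0.1 m/s from 0.4 to 0.6 m/s lowers the count by about 14% to 20% at a constant rate, and by about 6% to 12% even with a 10% better rate. These are changes within a patient under stated assumptions, not an estimate of bias in the trial's comparison.

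The reach is narrow. The primary SPPB outcome, dual-task gait velocity, MEC-Lobo, MOCA and TMT-A are not touched, and nothing here puts the trial's main conclusion at risk. It is a cheap improvement to one secondary measure, worth making before the dual-task cognitive results are compared between groups.

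**What to change.** Define the dual-task cognitive score, for both the verbal and the arithmetic condition, as correct responses per second: the number of responses divided by the walking time of the same attempt. State the stretch over which both are taken, either the timed 6 m or the full 8 m. Use this rate in any comparison between groups at 1 and 3 months, with its baseline value as covariate. Report the raw count and the walking time beside it, so that a trade between speed and cognition can be seen.

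The cost is a sentence in the outcome definition and one derived variable. Walking time is already needed to compute velocity, and no extra visit or test is required. There are two small downsides. Responses and time must be matched: the article does not say over which part of the 8 m responses are counted, so recording may need a minor adjustment, and data already collected may have to be checked for this. The rate may also slightly favour shorter walks if naming slows as the walk goes on.

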Considering the relation between frailty and cognition previously mentioned (Fig. 1), it makes sense that those interventions proved to be effective in frail elderly people could be also effective in the elderly with cognitive impairment, and vice versa. Although there are still few studies, some of them show how resistance exercise programmes during 12 weeks in older adults not only induce improvements in gait velocity but also improvements in executive functions [21] which are directly related to fall risk [22]. Additionally, recent research [23] has shown that, despite its limitations, multicomponent exercise can be one of the best approaches to improving functional capacity and executive functions and to decreasing fall risk and cognition in frail institutionalized elderly with cognitive impairment and dementia [22]. Other authors have found similar results in terms of reversing the frailty status and cognitive improvements in community-dwelling elderly without basal cognitive impairment [24].

In this context, the purpose of this study aims to examine whether an innovative multicomponent exercise programme called VIVIFRAIL [25–27] has benefits for functional and cognitive status among pre-frail/frail patients with MCI or dementia. VIVIFRAIL was developed by world experts in the field of physical exercise and frailty, and is considered an important step towards the novel era of precise prescription of physical activity [26, 27]. Recently, it has been proven safe and effective to reverse the functional decline associated with acute hospitalization in very old patients [28]. This programme is a significant step towards an individualized physical exercise programme [27] according to the functional capacity of each elderly person and includes specific recommendations on doses (intensity, volume and frequency), similar to other treatments applied to vulnerable populations, such as frail elderly individuals with cognitive complaints.

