### Study participants and eligibility criteria

The study will include outpatients of the Geriatrics Department of the Complejo Hospitalario of Navarra, the Matia Foundazioa in San Sebastian and the Hospital of Getafe (all three in Spain) older than 75 years of age between September 2017 and May 2019. Inclusion criteria include patients aged 75 years or older being capable and willing to provide informed consent, able to communicate and ambulate with or without personal/technical assistance, with a Barthel Index ≥ 60 and MCI or mild dementia according to DSM V criteria [31], level GDS-4 (Reisberg classification) [32], pre-frail or frail according to the Fried criteria [4] and having someone to help to supervise them when conducting the exercises.

The exclusion criteria include having any factor that precludes the performance of the physical training programme or testing procedures as determined by the attending physician. These factors, according to the VIVIFRAIL programme [26] include, but are not limited to, the following:myocardial infarction in the past 3 months;unstable angina pectoris;terminal illness;uncontrolled arrhythmia;unstable cardiovascular disease or other unstable medical condition;uncontrolled arterial hypertension;recent pulmonary thromboembolism;upper or lower extremity fracture in the past 3 months;institutionalized or pending entry into institution; andunwillingness to either complete the study requirements or to be randomized into the control or the intervention group.

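### The text and Table 1 disagree on who receives MEC-Lobo; if the text is followed, no global cognitive scale is common to all randomized patients

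*Protocol article*

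**What the plan says.** Only the protocol article is at hand. Its statements on this point are:

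- **Secondary outcomes (text).** The instruments for cognitive change are "MEC-Lobo) [42] in the case of dementia and the MOCA [43] in the case of MCI".
- **Table 1 (under Study design and setting).** The MoCA row reads "Montreal Cognitive Assessment (MOCA)—only for mild cognitive impairment" and is marked at screening, 1 month and 3 months. The MEC-Lobo row carries no such limit and is marked at baseline, 1 month and 3 months.
- **Eligibility.** Patients with "MCI or mild dementia according to DSM V criteria" enter the same trial. Randomization is simple 1:1, without stratification.
- **Aim (Background).** The question is whether the programme "has benefits for functional and cognitive status among pre-frail/frail patients with MCI or dementia".
- **Status of cognition.** The Primary outcome section states: "The primary outcome measure is the change in functional and cognitive status during the study period". The Abstract places it lower: "Secondary endpoints are changes in cognitive and mood status".
- **Analysis (Statistics and sample size).** Quantitative outcomes are analysed by ANCOVA of the post value on group with the pre value as covariate, by intention to treat.

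**The concern.** The two places give different instructions for the same visit. An assessor with an MCI patient at baseline cannot tell whether MEC-Lobo is due, and three centres could settle it in different ways.

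This decides which data exist, so an analysis plan written later can only partly repair it. Under the text, MCI patients have MoCA scores and dementia patients have MEC-Lobo scores. Raw scores on two different scales cannot enter one ANCOVA, so the whole-population question in the stated aim has no single global scale on which to be answered. Under Table 1 as naturally read, it has one. If practice differed between centres, MEC-Lobo would also be absent in some MCI patients for a reason unrelated to dropout, which the article's missing-data rules do not foresee.

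**Working it through.** **1. The passages side by side.**

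| | Text, Secondary outcomes | Table 1 |
|---|---|---|
| MoCA | MCI | MCI, stated in the row |
| MEC-Lobo | dementia | no restriction stated |

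The two agree on MoCA and differ on MEC-Lobo. Where Table 1 limits a test by diagnosis it says so ("only for mild cognitive impairment"), so an unmarked row is naturally read as applying to everyone.

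**2. Cognitive measures that are not split by diagnosis.** Trail Making part A (text, and Table 1 at all three visits), the dual-task cognitive counts (text), and the Isaacs Set Test (Table 1, baseline and 3 months). Each assesses a particular task or function; none is a global cognitive scale.

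**3. The plan's own sample size, reproduced first.** Inputs from Statistics and sample size: difference 1 point, SD 2.5, correlation 0.5, alpha 0.05 (two-sided assumed), power 90%.

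- n per group = 2 × 2.5² × (1 − 0.5²) × (1.960 + 1.282)² / 1² = 98.5, so 99 by the normal formula.
- With the noncentral t, 100 per group gives 90.15% and 101 gives 90.4%. The stated 101 is reproduced closely.
- 101 / 0.85 = 118.8, so 119 against the stated 120.

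**4. Illustration of the precision lost.** Two assumptions are not in the article: a cognitive effect equal to the SPPB planning effect (1/2.5 = 0.4 SD, with the same correlation of 0.5), and one diagnosis making up 30% to 70% of the sample. With residual SD 2.5 × √0.75 = 2.165:

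- power = Φ(1 / (2.165 × √(2/n)) − 1.96)
- difference detectable with 90% power, in SD units = √(2/n) × √0.75 × (1.960 + 1.282)

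| Share of sample | n per group | Power | Detectable difference |
|---|---|---|---|
| 100% | 101 | Φ(3.28 − 1.96) = 91% | 0.40 SD |
| 70% | 70.7 | Φ(2.75 − 1.96) = 78% | 0.47 SD |
| 50% | 50.5 | Φ(2.32 − 1.96) = 64% | 0.56 SD |
| 30% | 30.3 | Φ(1.80 − 1.96) = 44% | 0.72 SD |

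A noncentral-t calculation with 31 per group gives 43% in the last row.

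**5. If the strata are combined.** In SD units each stratum estimate has variance 0.75 × 2/n = 1.5/n, so its information is n/1.5. Inverse-variance weighting adds the two: (n₁ + n₂)/1.5 = 101/1.5. If the standardized effect is the same in both diagnoses, power returns to about 91%. The loss in step 4 therefore applies only when the strata are left separate.

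**The case against.** The strongest reply is that the passages can be read together: Table 1 schedules what is administered, and the text names the instrument used to judge change in each diagnosis. On that reading MEC-Lobo is already collected in everyone. This is possible, and it is true that Table 1 nowhere states that all patients receive MEC-Lobo; that is an inference from the missing restriction. But the article does not say which reading applies, so the need to reconcile stands.

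A reader might infer that the text version leaves no cognitive comparison in all randomized patients. The article does not support that: Trail Making part A, the dual-task counts and the Isaacs Set Test are not limited by diagnosis. What is missing is a common global scale.

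A reader might also infer that the within-diagnosis comparisons are invalid because randomization was not stratified. They are not. Diagnosis is an eligibility characteristic present before randomization, so each comparison is still randomized; the cost is balance and precision.

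It is also fair to say that the trial was sized on the SPPB alone, so a cognitive analysis cannot miss a power target the plan never set, and that choosing different tests for MCI and dementia is legitimate. A rule for combining two scales can be left to an analysis plan, so its absence here is not counted as a fault. These points limit the size of the concern but do not remove the contradiction.

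**Conclusion.** The contradiction is real and should be corrected. If the text is followed, the effect on global cognition in the whole MCI/dementia population cannot be estimated on one scale by the planned ANCOVA. This matters because cognition is in the stated aim and in the sentence defining the primary outcome.

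The power figures show scale only. They rest on an assumed diagnosis mix, on an effect size and correlation borrowed from the SPPB, and on the strata not being combined. They are not evidence that the trial is underpowered. The existing sample size is not disputed.

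**What to change.** 1. **Establish which version the sites have followed.** Recruitment began in September 2017 and was still open when the article appeared, so some MCI patients may have no baseline MEC-Lobo, and that value cannot be recovered.
2. **Bring the Secondary outcomes text into line with Table 1.** State that MEC-Lobo is given to all participants at baseline, 1 month and 3 months and analysed by ANCOVA in all randomized patients, adjusted for baseline score and diagnosis. Keep MoCA as a supplementary outcome within MCI.
3. **Where enrolled MCI patients lack a baseline MEC-Lobo,** prespecify a combination of the standardized within-diagnosis estimates (MEC-Lobo in dementia, MoCA in MCI).
4. **If one test per diagnosis was intended,** restrict the MEC-Lobo row of Table 1 and prespecify the same combination.

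Cost: the second step is a text correction and adds no test beyond those Table 1 already schedules, although sites that followed the text would have to start giving MEC-Lobo to MCI patients. The downside is a possible MEC-Lobo ceiling in MCI, which the supplementary MoCA partly covers. The combined analysis rests on treating standardized effects on two different scales as comparable, so it is second best to a common scale.
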